### Intervention

Women who meet the inclusion criteria will be recruited in the study using a non-probability convenience sampling method. Women in the intervention group will be included in the study after their first pregnancy visit (6–10 weeks of gestation) and will receive continuous care by midwifery students. Women in the control group will receive the usual and routine care, and will be included in the study at the time of delivery. They will have a gestational age of more than 37 weeks based on the inclusion criteria of the study. Their delivery will be performed by midwifery students who will follow them up until six weeks after delivery.

At first, the necessary training will be given by the lead researcher (FR) to the students in orientation sessions held for both groups separately. In the intervention group, each midwifery student as the main midwife will be responsible for taking care of two or three pregnant women and will be the back-up midwife for two other pregnant women (under the supervision of other students). The lead researcher will create a group in WhatsApp with the participation of students in the intervention group, and they can communicate with each other and the researcher. Also, the midwifery students will be directly and indirectly under the supervision of a qualified person (lead researcher). Another WhatsApp group will be created for the women of the intervention and control groups (to facilitate communication between the researcher and the women). Two midwifery students will be introduced to each pregnant woman in the intervention group (as a main midwife and a backup midwife). If the main midwife is not available, the woman will be in contact with the backup midwife. The backup student will meet the woman at least once and will be introduced to her.

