### Follow-up

The students in the intervention group will start prenatal care < 20 weeks of gestation. At least five round of prenatal care will be provided by each student according to national guidelines for each pregnant woman. Pregnant women can communicate with their in-charge students in non-emergency cases from 8:00 a.m. to 23:00 p.m. and in emergency cases 24 h a day, all days a week. All reports will be recorded by the students. During labor and delivery, the student and the lead researcher will be present at the mother's bedside. In case of natural vaginal delivery (NVD), delivery will be done by a student midwife under the supervision of the researcher. In case of cesarean delivery (CS), a student will be present at the patient's bedside. Postpartum care will be provided by midwifery students in both groups (intervention and control). Each student will be at the mother's bedside for two hours after delivery. The conditions of labor, delivery, and the neonate will be recorded by the student in the relevant form. Also, the mother will be followed up by telephone for up to 6 weeks after delivery (postpartum). The clinical competency questionnaire will be completed by students before and after the intervention.

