### Inclusion criteria

Inclusion criteria for midwifery students will be: studying at the seventh and eighth semester and willingness to participate in the study.

Inclusion criteria for service recipients (pregnant women) will be: age 18 – 40 years, Iranian nationality, singleton pregnancy, low risk pregnancy, and gestational age < 20 wks.

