### Exclusion criteria

Exclusion criteria will be: history of psychiatric disorders, previous caesarean section, use of alcohol and tobacco, or having a disease that requires prenatal care by a specialist.

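### Control women enter at delivery beyond 37 weeks and intervention women in early pregnancy, so preterm births and pregnancy losses can occur in the intervention arm only

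*Protocol article*

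**What the plan says.** All statements are in the Protocol article.

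- **Intervention, intervention arm:** women join "after their first pregnancy visit (6–10 weeks of gestation" and receive continuous care from then on.
- **Intervention, control arm:** women "will be included in the study at the time of delivery". The section adds: "They will have a gestational age of more than 37 weeks based on the inclusion criteria of the study".
- **Follow-up:** "The students in the intervention group will start prenatal care < 20 weeks of gestation".
- **Inclusion criteria (quantitative phase):** one list for all women, including "singleton pregnancy, low risk pregnancy, and gestational age < 20 wks". It has no lower limit on gestational age and no criterion of more than 37 weeks.
- **Exclusion criteria:** these include "having a disease that requires prenatal care by a specialist". The article does not say at what point in pregnancy this, or low-risk status, is judged for control women.
- **Data analysis:** t-tests, chi-square tests, and ANCOVA for confounders that are not named. No common analysis set is defined for the two arms.

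**The concern.** A control woman included at delivery beyond 37 weeks cannot at that moment meet a criterion of less than 20 weeks. The term condition attributed to the inclusion criteria is not among them. This is a contradiction in eligibility, not a detail that a condensed article leaves to a fuller document.

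It also has a statistical consequence. Control women are selected on having reached term, and intervention women are not. The arms then differ by construction in outcomes that depend on gestational age, even if the programme has no effect. ANCOVA cannot repair this, because the control arm holds no preterm births from which an adjustment could be estimated. At stake is the second specific objective, the effect on pregnancy outcomes.

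**Working it through.** **Step 1: what each arm can contain.**

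| Event | Intervention arm | Control arm |
|---|---|---|
| Pregnancy loss after early-pregnancy entry | possible | impossible (entry is at delivery) |
| Birth before 37 weeks | possible (no rule against it) | impossible (more than 37 weeks required) |
| Pregnancy that becomes high-risk before delivery | possible (no rule removes the woman) | excluded only if low-risk status is judged at delivery, which is not stated |
| Complication arising in labour | possible | possible |

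The first two rows follow directly from the text. The third is an inference.

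**Step 2: outcomes affected.** The listed secondary outcomes include NICU admission and Apgar score, where the link to preterm birth is plainest. Mode of delivery, induction, labour length and breastfeeding may also be affected, but no size is computed for them here.

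**Step 3: illustration with no true effect.** The article gives no preterm or NICU rates, so these are assumptions:

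- r_term = 4% NICU admission among term babies
- q = 5% to 10% of intervention women delivering preterm
- r_pre = 30% to 50% NICU admission among preterm babies
- 29 women per arm (Sample size section)

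Expected intervention-arm risk = q × r_pre + (1 − q) × r_term. Expected control-arm risk = r_term = 4.0%.

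| q | r_pre | Calculation | Intervention | Control | Extra babies among 29 |
|---|---|---|---|---|---|
| 5% | 30% | 0.05 × 0.30 + 0.95 × 0.04 | 5.3% | 4.0% | 29 × 0.013 = 0.4 |
| 5% | 50% | 0.05 × 0.50 + 0.95 × 0.04 | 6.3% | 4.0% | 29 × 0.023 = 0.7 |
| 10% | 30% | 0.10 × 0.30 + 0.90 × 0.04 | 6.6% | 4.0% | 29 × 0.026 = 0.8 |
| 10% | 50% | 0.10 × 0.50 + 0.90 × 0.04 | 8.6% | 4.0% | 29 × 0.046 = 1.3 |

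The expected number of preterm births among 29 is 29 × 0.05 = 1.5 to 29 × 0.10 = 2.9. The chance of at least one is 1 − 0.95^29 = 77% to 1 − 0.90^29 = 95%.

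**Step 4: wider assumptions.** Let q also cover pregnancies that became high-risk, up to 30%, with a 5% risk in the remaining women and 30–50% in these. The spurious difference then runs from 0.05 × (0.30 − 0.05) = 1.2 percentage points (q = 5%) to 0.30 × (0.50 − 0.05) = 13.5 points (q = 30%). The upper end depends on the inference in the third row of the first table.

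**The case against.** Several stronger readings are tempting, and the document does not support them.

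- **The 6–10 week and under-20-week statements contradict each other.** They need not. The first range lies inside the second, and the bracket may date the first visit rather than entry. The firm conflict is more than 37 weeks for controls against less than 20 weeks for everyone.
- **Pregnancies that turned high-risk are certainly confined to the intervention arm.** This depends on when low-risk status is judged for control women, and the article does not say. Judging it at inclusion, that is at delivery, is the natural reading but remains an inference.
- **The bias must run against the programme.** That is likely if all enrolled intervention women are analysed. If complicated pregnancies leave the arm, within the 20% dropout allowed for, the direction is unclear.
- **The trial's main result is invalid.** The primary outcome is student competence, which this does not directly affect.
- **The distortion is a doubling.** A ratio of that order arises only with both assumed rates at the top of their ranges, and in counts it is little more than one baby.

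It can also be said that the women's comparison is already non-randomised, because the arm is set by hospital and women are a convenience sample. That is true, but it is a separate bias. Unequal entry would distort these outcomes even if women were allocated perfectly.

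None of this removes the core: the article restricts one arm to term and not the other, and it states no common analysis set.

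**Conclusion.** The point holds for the secondary maternal and neonatal outcomes. The entry rule for control women contradicts the inclusion criteria. As written, preterm births and losses after entry can occur in the intervention arm only; the same is probable, but inferred, for pregnancies that become high-risk before delivery. Under the assumed rates, NICU admission would show 5.3–8.6% against 4.0% with no true effect. That is small in absolute count, but it matters because rare outcomes in arms of 29 turn on one or two babies. The size rests wholly on assumed rates, and the direction on who is analysed.

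**What to change.** **Preferred.** Reconcile the Intervention and Inclusion criteria sections so that both arms have the same entry rule. Register control women at the participating health centres before 20 weeks, leave them in routine care and collect their outcomes at delivery. This costs consent at an antenatal visit and a wait of at least 37 − 20 = 17 weeks from registration to term. The control phase is planned to come first and sampling is already in process, so the decision is needed soon.

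**Fallback, if control inclusion at delivery stays.** Define the between-arm comparison as women in either arm who reach more than 37 weeks and meet the same eligibility criteria at admission. State when low-risk status is judged. Report losses, preterm births and other earlier events in the intervention arm separately. Limit the conclusion to term births.

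The fallback is cheap in wording but has three real costs:

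- It loses intervention women: about 1.5 to 2.9 of 29 if 5–10% are ineligible at term. At an assumed 20–30% it loses 5.8 to 8.7, leaving about 23 to 20 before other dropout, against the plan's own requirement of 23.
- It cannot show any effect on preterm birth or pregnancy complications.
- It conditions on a state that the programme may itself change, which can introduce a new selection.

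Neither option cures the separate bias from assigning women by hospital.

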### Randomization

To implement the intervention, the students will be divided into two intervention (providing continuous care for pregnant women) and control (providing standard care for pregnant women) groups. Allocating students will be done using permuted block randomization technique with a block size of four and an allocation ratio of 1:1. Five blocks of 4 pieces and 3 blocks of 3 pieces will be extracted randomly using WIN PEPI software. In each block of 4, 2 students will be in control and 2 will be in intervention group. Also, in each block of 3 students, 1 student will be in control and 2 will be in intervention group, and the arrangement of each person is random. To prevent contamination, first the control group will provide routine care, and then the intervention group will conduct continuity of care for pregnant women. Mothers are randomly selected based on the hospital where they will give birth. As a result, Razi Hospital will be the control group and Sina Hospital will be the intervention group.

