### Secondary outcome

Mode of delivery, length of labor stages, the need to induction, postpartum bleeding first and fifth minute Apgar score, admission of neonate to the neonatal intensive care unit, breastfeeding initiation, and exclusive breastfeeding up to 6 weeks postpartum.

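### A single WhatsApp group for women of both arms is out of step with a plan that otherwise separates them: a minor, avoidable risk to secondary outcomes

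*Protocol article*

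**What the plan says.** All references are to the protocol article.

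- **Women's chat (Intervention).** "Another WhatsApp group will be created for the women of the intervention and control groups". Its stated purpose is "to facilitate communication between the researcher and the women". Nothing is said about who may post, what may be posted, or when a woman leaves.
- **Students' chat (Intervention).** "The lead researcher will create a group in WhatsApp with the participation of students in the intervention group". Control students are not included.
- **Orientation (Intervention).** Training is given in "orientation sessions held for both groups separately".
- **Order and site (Randomization).** "To prevent contamination, first the control group will provide routine care, and then the intervention group will conduct continuity of care for pregnant women". Razi Hospital supplies the control women and Sina Hospital the intervention women.
- **Entry and follow-up (Intervention, Follow-up, Inclusion criteria).** Intervention women enter after a first visit at 6–10 weeks of gestation; the other two sections say under 20 weeks. Control women enter at delivery, beyond 37 weeks. Mothers are followed by telephone to 6 weeks postpartum.
- **Outcomes.** The primary outcome is the students' clinical competence. The secondary outcomes are obstetric and neonatal, and end with breastfeeding initiation and "exclusive breastfeeding up to 6 weeks postpartum".

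**The concern.** The authors restrict a channel to one arm when they mean to: the students' chat and the orientation sessions are both limited in this way. The women's chat is the one channel described that brings the arms together, and it has no safeguard.

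Two effects are possible. Advice passed between mothers could move a behavioural outcome in one arm toward the other and so shrink the estimated difference. Separately, women who see how the other arm is cared for might answer differently when telephoned, and the direction of that effect cannot be predicted. Exclusive breastfeeding is the clearest candidate for both, because it depends on behaviour and remains open for six weeks after birth.

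**Working it through.** The plan gives no figure on this point, so the check sets the sections side by side.

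**1. One chat or two?** The sentence has a singular group and names both arms as its members. One group per arm is a possible reading, but it strains the wording.

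**2. Intervention to control.** A control woman is exposed only from delivery to 6 weeks postpartum, and only if intervention women are already in the chat. The Randomization section puts control care first. The Intervention section makes six-week follow-up part of the control students' work. Together these suggest that control follow-up comes before the intervention phase. No sentence says that the last control follow-up ends before the first intervention woman is enrolled, and no gap is given.

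The timing also limits what could be passed on. Take delivery at 37 weeks or later (an assumption; the article gives 37 weeks only for control women). The wait from an intervention woman's enrolment to her delivery is then at least:

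- entry at 10 weeks: 37 − 10 = 27 weeks
- entry at 6 weeks: 37 − 6 = 31 weeks
- entry just under 20 weeks: 37 − 20 = 17 weeks

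For intervention mothers to share their own feeding experience with controls under follow-up, the phases would have to overlap by about 17 to 31 weeks or more. A shorter overlap would expose controls only to what pregnant intervention women say about their care.

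**3. Control to intervention.** This direction does not need overlapping follow-up, only that earlier control women stay in the chat. No rule removes them. Intervention women enter early in pregnancy, so all their delivery, neonatal and feeding outcomes are still ahead.

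**4. Outcomes exposed in the control arm.** Mode of delivery, length of labour, induction and Apgar score are essentially settled when a control woman enters, and NICU admission can hardly be moved by a chat. Breastfeeding initiation follows birth closely and leaves little time for influence. What remains is mainly exclusive breastfeeding to 6 weeks, and the telephone reports.

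**5. Primary outcome.** It is measured on students, and the article does not list students as members of the women's chat.

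**6. Size, as a conditional illustration only.** The article gives no breastfeeding rates and no degree of contact. Assume exclusive breastfeeding of 60% v 30%, 29 women per arm (the planned number, no dropout) and a two-sided 5% test. With p̄ the mean of the two proportions,

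power = Φ{[|p₁ − p₂|√n − 1.96√(2p̄(1 − p̄))] / √(p₁(1 − p₁) + p₂(1 − p₂))}.

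| Share of gap closed | Rates | Calculation | Power |
|---|---|---|---|
| 0% | 60% v 30% | (1.616 − 1.379)/0.671 = 0.353 | 63.8% |
| 10% | 60% v 33% | (1.454 − 1.383)/0.679 = 0.105 | 54.2% |
| 20% | 60% v 36% | (1.292 − 1.385)/0.686 = −0.135 | 44.6% |

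The first row is also the case with no overlap, where the loss for controls is nil or close to it. The other rows show only how the loss would scale if contact did close part of the gap.

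**The case against.** The strongest reply is that the stated order already does the work. Control care comes first and includes the six-week follow-up, so control women would have finished before the programme starts. The chat exists for contact with the researcher, and care itself is delivered through named students and visits. Membership and posting rules are also details that an article may leave to the full protocol.

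Much of this stands. If the order is kept strictly, the route to controls is practically closed. The argument from condensation does not remove the point, because the article states a shared chat; it is not silent on the matter. The order also does not cover the opposite direction, from control women who remain members to intervention women still in pregnancy.

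Three stronger readings are not supported:

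- A reader might infer that the shared chat defeats the plan's own anti-contamination step. That step orders the care given by the two student groups. It does not address contact between women, so the two statements are out of keeping with each other but not contradictory.
- A reader might infer that control mothers will read programme material. Nothing says that such material is posted in the chat.
- A reader might take the power figures as the expected loss. They rest on assumed rates and assumed contact.

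**Conclusion.** The point holds as a minor design weakness. On its natural reading, the article puts women of both arms in one chat, without safeguards, in a plan that otherwise separates them by training, student chat, hospital and time. Influence on controls requires overlap that the text neither states nor excludes. It would bear mainly on exclusive breastfeeding to 6 weeks and on telephone reports, and is near zero if the phases do not overlap. Influence on intervention women requires only that earlier control women stay in the chat. Student competence is not directly affected. The size cannot be derived from the documents. The conclusion rests on reading the chat sentence as one group; if one per arm was meant, a clarified sentence settles the matter.

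**What to change.** In the Intervention section, replace the shared chat with a separate WhatsApp group for each arm, or with one-to-one or researcher-only messages. State that women of both arms are never placed in one chat and that both arms receive the same neutral logistics messages. If one group per arm was already intended, say so.

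The Study status section reports that quantitative sampling is in process. If a shared chat already exists, split it now and record the dates on which women of both arms were members together, so that any overlap can be reported.

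The cost is one more chat to manage and a change of wording. Sample size, analysis and care are unchanged.

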### Instruments

All students and pregnant women participating in this study will complete a demographic questionnaire. A checklist will be provided for collecting data during prenatal care, labor, and delivery.

Also, the midwifery students will complete the clinical competency questionnaire at the beginning and end of the study.

Care will be provided and recorded by the main student according to the pregnancy care protocol. Also, danger signs will be taught to the students according to the national protocol, and emergencies will be handled by the midwifery student under the supervision of the lead researcher. Admission to hospital will be arranged by the student, and all information will be recorded. Pregnancy, labour and delivery, postpartum, and newborn checklist will be completed. Students will complete a demographic and obstetric questionnaire that includes questions about age, education, occupation, gravidity, parity, abortions, live and dead children, last contraceptive method, intended and unintended pregnancies, last menstrual period (LMP), gestational age, date of birth, body mass index (BMI), previous pregnancy and childbirth records, high-risk behavior of the mother and father, current history of special care, test and ultrasound results, and participation in childbirth preparation class. Also, the following data will be recorded in the labor and delivery and post-partum checklist: checking the conditions of labor according to the partograph, length of labor, need for induction and the method used type of delivery, examination of perineal trauma, postpartum bleeding, and examination of the condition of the mother up to 6 weeks after delivery. In addition, the amount of bleeding will be checked visually and by measuring the level of hemoglobin and hematocrit. Apgar score of the newborn will be recorded (in infant checklist) in minutes 1 and 5. Also, the newborn’s hospitalization status, breastfeeding and anthropometric indices will be recorded.

### Follow-up

The students in the intervention group will start prenatal care < 20 weeks of gestation. At least five round of prenatal care will be provided by each student according to national guidelines for each pregnant woman. Pregnant women can communicate with their in-charge students in non-emergency cases from 8:00 a.m. to 23:00 p.m. and in emergency cases 24 h a day, all days a week. All reports will be recorded by the students. During labor and delivery, the student and the lead researcher will be present at the mother's bedside. In case of natural vaginal delivery (NVD), delivery will be done by a student midwife under the supervision of the researcher. In case of cesarean delivery (CS), a student will be present at the patient's bedside. Postpartum care will be provided by midwifery students in both groups (intervention and control). Each student will be at the mother's bedside for two hours after delivery. The conditions of labor, delivery, and the neonate will be recorded by the student in the relevant form. Also, the mother will be followed up by telephone for up to 6 weeks after delivery (postpartum). The clinical competency questionnaire will be completed by students before and after the intervention.

